#### Functional Data Preprocessing

For each BOLD run per subject (across all tasks and sessions), the following preprocessing will be performed. First, a reference volume and its skull-stripped version will be generated using a custom methodology of *fMRIPrep*. The BOLD reference will then be co-registered to the T1w reference using bbregister (FreeSurfer) which implements boundary-based registration (65). Co-registration will be configured with nine degrees of freedom to account for distortions remaining in the BOLD reference. Head-motion parameters with respect to the BOLD reference (transformation matrices, and six corresponding rotation and translation parameters) are estimated before any spatiotemporal filtering using mcflirt [(FSL 5.0.9, (66)]. The BOLD time-series (including slice-timing correction when applied) will be resampled onto their original, native space by applying a single, composite transform to correct for head-motion and susceptibility distortions. These resampled BOLD time-series will be referred to as *preprocessed BOLD in original space*, or just *preprocessed BOLD*. The BOLD time-series are resampled to MNI152NLin2009cAsym standard space, generating a *preprocessed BOLD run in MNI152NLin2009cAsym space*. First, a reference volume and its skull-stripped version are generated using a custom methodology of *fMRIPrep*. Several confounding time-series are calculated based on the *preprocessed BOLD*: framewise displacement (FD), DVARS and three region-wise global signals. FD and DVARS are calculated for each functional run, both using their implementations in *Nipype* [following the definitions by Power and colleagues (67)]. The three global signals are extracted within the CSF, the WM, and the whole-brain masks. Additionally, a set of physiological regressors re extracted to allow for component-based noise correction [*CompCor*, (68)]. Principal components are estimated after high-pass filtering the *preprocessed BOLD* time-series (using a discrete cosine filter with 128s cut-off) for the two *CompCor* variants: temporal (tCompCor) and anatomical (aCompCor). Six tCompCor components are then calculated from the top 5% variable voxels within a mask covering the subcortical regions. This subcortical mask is obtained by heavily eroding the brain mask, which ensures it does not include cortical GM regions. For aCompCor, six components are calculated within the intersection of the aforementioned mask and the union of CSF and WM masks calculated in T1w space, after their projection to the native space of each functional run (using the inverse BOLD-to-T1w transformation). The head-motion estimates calculated in the correction step are also placed within the corresponding confounds file. The BOLD time-series, are resampled to surfaces on the following spaces: *fsaverage5*. All resamplings can be performed with *a single interpolation step* by composing all the pertinent transformations (i.e., head-motion transform matrices, susceptibility distortion correction when available, and co-registrations to anatomical and template spaces). Gridded (volumetric) resamplings will be performed using antsApplyTransforms (ANTs), configured with Lanczos interpolation to minimize the smoothing effects of other kernels (69). Non-gridded (surface) resamplings were performed using mri_vol2surf (FreeSurfer).

Many internal operations of *fMRIPrep* use *Nilearn* 0.4.2 (70), mostly within the functional processing workflow. For more details of the pipeline, see the section corresponding to workflows in *fMRIPrep*’s documentation.

Structural measures of total gray matter volume, white matter volume, cortical surface area, and average cortical thickness will be extracted from FreeSurfer (run during preprocessing). After preprocessing, independent component analysis (ICA) will be conducted using FSL’s MELODIC software to examine intrinsic connectivity networks in r-fMRI. ICA is a statistical technique that separates a set of signals into independent spatiotemporal components (71). It allows for the removal of artifact and the isolation of neural networks (72, 73). We will allow the software to estimate the optimal number of components for each subject. Components will be transformed to standard space, and the DMN and SN will be selected from among each subject’s independent components using an automated template-matching procedure (73). A one-sample t-test will be performed on normalized network maps. These maps will be used to generate connectivity scores for each ICN.

Condition effects for the task-based fMRI will be estimated using the general linear model. The response to events will be modeled by a canonical hemodynamic response function (HRF). The task switching task has two events of interest: task-switch events and task-repeat events contrasted with each other, as well as two blocked conditions: mixed-task blocks and single-task blocks in another contrast. The food image task has two events of interest: food images and non-food images contrasted with each other. Condition-specific estimates of neural activity (betas, corresponding to the height of the HRF) will be computed independently at each voxel for each subject. Analyses will be conducted in FSL FEAT, which utilizes cluster-based thresholding and Gaussian Random Field (GRF) theory to identify significant clusters of voxels for each analysis. Although we have hypotheses related to certain brain regions, we will conduct whole brain analyses to ensure we are not biasing results.

DTI data will be analyzed with FSL Diffusion Toolbox (FDT) to perform affine registration to correct for eddy current distortions, extract brain from skull in the image, and fit tensors and tracts to the data. Further tensor fitting and fiber tracing will be completed with Diffusion Toolkit software. Primary measures will be of fractional anisotropy (the degree to which diffusion takes place in a given direction) and R1 (measure of relaxation rates of water protons, which has a strong relation with myelin content). Probabilistic tractography will be explored using FSL’s built-in tools, particularly along fronto-striatal pathways, which may be impacted in AN (74). Of note, DTI data, as well as structural data, can be impacted by effects of dehydration, which may relate to malnutrition (75). Although objectively assessing hydration status specifically would be ideal, it is not possible in this small study. However, we will include reports of hydration, as well as recent hospitalizations, as many of the patients in the trial were in the hospital for medical stabilization (including hydration) prior to enrolling in the study.

Behavioral data from the risk-taking task will be examined by calculating the adjusted score, which is the average number of casts taken on rounds when participants chose to stop fishing. Higher scores indicate greater risk-taking.

Across all measures (gray and white matter volume, cortical surface area, cortical thickness, r-fMRI connectivity for SN and DMN, DTI FA and R1, task-based contrasts, and risk-taking scores), we will examine change over time using repeated measures analyses, including mixed effects modeling for extracted scores or repeated measures modeling in FSL for task-based measures. Because EOT will occur at different times after baseline depending on treatment duration, time will be included as a covariate. Primary comparisons will be conducted between those who gain 2.4 kg by session 4 and those who do not (early responders vs. non-early responders). We will also use weight change as a continuous variable to examine how change in the brain and behavior measures is associated with weight change, particularly if we have small cell size in one of the two responder groups. Exploratory analyses will also examine baseline brain and behavior measures as predictors of early response and end of treatment outcome *via* mixed effects.

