### Specific Aims and Hypotheses

Overall, the study aims to examine the neural correlates of early weight gain in adolescents with AN undergoing FBT with MRI scans conducted at baseline prior to initiating treatment, after session 4 (the point at which weight gain is predictive of clinical EOT response), and again at EOT (18 sessions of treatment, approximately 6 months with a maximum of 9 months). Although this study is designed to provide evidence of feasibility in conducting neuroimaging in the context of FBT and establish preliminary effect sizes to guide future research, we provide the following specific hypotheses that we hope to explore in this pilot study. We hypothesize greater increases in brain volumes, surface area, and cortical thickness from pre-treatment to session 4 in those who gain more than 2.4 kg during that time. We also hypothesize that network connectivity and activity during r-fMRI will show greater changes in adolescents with early weight gain compared to those who do not show early weight gain. Specifically, we predict greater increases in default mode activity and reductions in SN activity from pre-treatment to session 4 in those who gain more than 2.4 kg during that time (47). We also hypothesize improvements in white matter integrity, measured with DTI, in those who gain more than 2.4 kg by session 4 compared to those who do not, providing evidence that consistent nutritional improvements can have rapid impact on brain connectivity (48). We also hypothesize improvements in functional tasks related to cognitive and emotional functioning in those who gain more than 2.4 kg by session 4. Specifically, we expect improvements in a task-switching task as evidenced by improved behavioral performance and altered brain activity in prefrontal cortex and superior parietal cortex. During a food image task, we expect to find reduced amygdala activity in response to food versus non-food images over time in those who show early weight gain. Although the primary aim relates to neural changes at session 4 (the time where early weight gain is predictive of outcome), a secondary aim is to examine these measures at EOT, which will allow us to capture any neural changes that may be more delayed, requiring longer length of time or more weight gain for recovery. This secondary aim is in place due to the preliminary nature of the protocol, since there is no prior research related to early treatment effects. In other words, this aim increases the likelihood to detect effects given that prior research on weight restoration in AN has shown improvements across these domains.

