Because participants will be recruited for the neuroimaging study prior to the start of treatment, we cannot balance the numbers of participants in a particular treatment arm. All study participants who meet eligibility criteria and are able to visit Stanford University for three imaging appointments will be invited to participate. Although the main RCT is being conducted at two sites (Stanford University and University of California, San Francisco), they are both located in the San Francisco Bay Area, and thus, are both potential sites for the recruitment of participants for this neuroimaging component. The population of the Bay Area is large and diverse, and the RCT makes specific efforts to recruit minorities for the study. The target sample size for this preliminary study is 20 in order to establish feasibility of including neuroimaging to an RCT of FBT and obtain preliminary effect sizes. Inclusion criteria include: 12–18 years of age that meet DSM-5 criteria for AN and participating in the RCT testing IPC for early non-response to FBT. Exclusion criteria include: 1) associated physical illness that necessitates hospitalization; 2) psychotic illness or other mental illness requiring hospitalization; 3) current dependence on drugs or alcohol; 4) physical conditions (e.g., diabetes mellitus, pregnancy) known to influence eating or weight; 5) Wechsler Abbreviated Scale of Intelligence (WASI) scores below the low average range defined by the test (<80); 6) family history or current child abuse or neglect (when reported in response to a question on phone screen, the perpetrator of abuse is excluded from family treatment, but the adolescent may participate with the rest of the family); 7) previous FBT for AN; 8) contraindications for MRI (e.g., orthodontia, metallic implants); 9) current or past major neurological (e.g., seizure disorder, psychosis, head trauma) or major sensory deficit. Participants are withdrawn from the study if any of the following occur: 1) sexual or physical abuse by a family member; 2) hospitalization for >21 days; 3) missing >4 consecutive appointments; worsening of psychiatric conditions such that participant would be clinically better served by referral for other treatment; 4) participant undertaking other psychotherapies during the treatment study. Visual acuity is determined by self-report, and participants with corrected vision use MR-safe lenses during scans.

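### The amygdala, prefrontal and parietal hypotheses are left to whole-brain cluster inference on a mistaken bias argument, and no regional estimate is named

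*Protocol article*

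**What the plan says.** In the protocol article, Specific Aims and Hypotheses ties the task-fMRI predictions to named regions. The prediction for the pictures of food reads: "we expect to find reduced amygdala activity in response to food versus non-food images over time in those who show early weight gain". For task switching, the prediction is "altered brain activity in prefrontal cortex and superior parietal cortex", without a direction.

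The Data Analytic Plan (task-fMRI text under Functional Data Preprocessing) assigns the analysis to FSL FEAT, which "utilizes cluster-based thresholding and Gaussian Random Field (GRF) theory to identify significant clusters of voxels for each analysis". It then adds: "Although we have hypotheses related to certain brain regions, we will conduct whole brain analyses to ensure we are not biasing results". The closing paragraph of the plan uses mixed models for extracted scores and FSL repeated-measures models for the task measures. No regional or small-volume test is named.

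The purpose matters here. Specific Aims says that the pilot is meant to "establish preliminary effect sizes to guide future research", and Participants gives the reason for a target of 20 as to "establish feasibility of including neuroimaging to an RCT of FBT and obtain preliminary effect sizes".

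**The concern.** Regional bias arises when a region is picked because the same data show an effect there. A region taken from earlier literature and an anatomical atlas, before any scan is analysed, carries no such bias. Searching the whole brain therefore removes no bias. It gives up the prior information and pays for a search over the full brain volume.

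Two things are at stake. First, cluster inference requires a run of supra-threshold voxels of a minimum volume, which is hard on a small structure, so a true amygdala effect may be missed more often than necessary. Second, the only task-fMRI output that the article describes is significant clusters. A pilot that is meant to supply effect sizes needs an estimate that exists whether or not a threshold is passed.

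**Working it through.** The article states no power, alpha, effect size, cluster-forming threshold or smoothing for the task analyses, so there is no planned figure to reproduce. What follows is illustrative.

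**Inputs from the article.** Total n = 20. The main comparison is early responders versus non-early responders. Field of view is 22 cm, matrix 64 × 64, slices 4.0 mm with a 0.5 mm gap.

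**Assumptions.** Split 10/10 (5/15 as a variant). Amygdala 1.2–1.8 cm³ per side. Search volume 1.2–1.4 litres. Smoothness (FWHM) 6–12 mm. Cluster-level alpha 0.05. Cluster-forming threshold Z>2.3 or Z>3.1.

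**1. Voxels in the amygdala.** Voxel volume including the gap = (220/64)² × 4.5 = 53.2 mm³. Then 1200/53.2 ≈ 23 and 1800/53.2 ≈ 34 voxels.

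**2. Minimum significant cluster (Gaussian random field).** With R = V/FWHM³:
- expected number of clusters, Em = R(4 ln 2)^1.5 (2π)^−2 (u² − 1) exp(−u²/2)
- expected supra-threshold volume, EN = R·P(Z>u)
- β = (Γ(2.5)·Em/EN)^(2/3)
- critical extent k = [ln(Em/(−ln 0.95))/β]^1.5, in units of FWHM³

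Example: u = 2.3, FWHM 8 mm, V = 1.2 litres gives R = 2343.75, Em = 83.5, EN = 25.1, β = 2.69, k = 4.55, so 4.55 × 512 ≈ 2330 mm³.

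| FWHM | Z>2.3 (1.2 / 1.4 L) | Z>3.1 (1.2 / 1.4 L) |
|---|---|---|
| 6 mm | 1.16 / 1.19 cm³ | 0.34 / 0.35 cm³ |
| 8 mm | 2.33 / 2.41 cm³ | 0.65 / 0.68 cm³ |
| 10 mm | 3.95 / 4.09 cm³ | 1.07 / 1.11 cm³ |
| 12 mm | 6.01 / 6.24 cm³ | 1.56 / 1.64 cm³ |

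At Z>2.3 with FWHM of 8 mm or more, activation confined to one amygdala could not reach significance. At Z>3.1 the extent is mostly attainable, but the height is hard to reach.

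**3. Height: one voxel against one regional mean.** Two-sample t on change scores, with noncentrality d/√(1/n₁ + 1/n₂) and 18 df. At 10/10 and d = 0.8 the noncentrality is 0.8/√0.2 = 1.79. The critical t is 2.10 (two-sided 5%), 2.52 (Z>2.3) and 3.63 (Z>3.1).

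| 10/10 | d=0.5 | d=0.8 | d=1.0 | d=1.2 |
|---|---|---|---|---|
| One ROI mean, two-sided 0.05 | 0.18 | 0.40 | 0.56 | 0.72 |
| ROI mean, Bonferroni for 3 | 0.09 | 0.23 | 0.37 | 0.53 |
| Voxel crosses Z>2.3 | 0.10 | 0.26 | 0.41 | 0.57 |
| Voxel crosses Z>3.1 | 0.02 | 0.06 | 0.13 | 0.22 |

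At 5/15 and d = 0.8 the ROI mean has power 0.31. The voxel crosses with probability 0.19 (Z>2.3) or 0.04 (Z>3.1). The voxel figures precede the extent requirement.

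**4. Effect sizes, if read only when significant.** At 10/10 the smallest observed d that can cross is 2.52 × √0.2 = 1.13 (Z>2.3) or 3.63 × √0.2 = 1.62 (Z>3.1). In simulation (1,000,000 draws), a true d of 0.8 averages 1.47 or 1.91 among the crossings. A later two-group trial with 80% power at two-sided 5% needs about 26 per group for d = 0.8, but about 9 for 1.47 and 6 for 1.91. A regional mean reported regardless of its p-value averages 0.84. The same mean reported only when significant averages 1.32.

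**The case against.** Whole-brain inference with family-wise correction is a recognised choice. The article is a condensed account of a pilot that claims no power: "The target sample size for this preliminary study is 20 in order to establish feasibility". The full plan could contain a regional summary, and voxelwise betas are computed for every subject, so unthresholded estimates can be extracted.

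Several stronger readings are tempting and are not supported:
- **That the amygdala hypothesis is almost certain to fail.** A voxel crosses Z>2.3 with probability 0.57 at d = 1.2, and at 6 mm smoothness the minimum cluster is within the assumed amygdala volume at both thresholds. A cluster may also extend into adjacent tissue. Threshold, smoothing and effect size are all assumed.
- **That the plan yields inflated effect sizes.** Nothing says that estimates will be taken from significant clusters. Inflation comes from selecting on significance, and it affects a regional mean too if that is reported selectively.
- **That the same loss applies to all three regions.** The minimum-volume argument is specific to the amygdala. Prefrontal and parietal cortex are large, and averaging over either could hide a focal effect.
- **That whole-brain testing is the cause of the low power.** Most of it comes from n = 20: one regional test has power of only 0.40 at d = 0.8. With Bonferroni for three regions, 0.53 at d = 1.2 is below the 0.57 for crossing Z>2.3, before the extent rule is applied.

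These points limit the size of the concern. They do not rescue the stated reason, which is explicit in the text and is not a detail left to another document.

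**Conclusion.** The concern holds in limited form. The article sets its own regional hypotheses aside for a reason that is wrong, and it names no regional estimate although effect sizes are a purpose of the study.

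For the amygdala, the loss against a single pre-specified regional test can be large: 0.40 against 0.26 or 0.06 at 10/10 and d = 0.8, with a further extent requirement of about 0.34–6.2 cm³. This rests on the assumed threshold, smoothing, split and amygdala volume, and on the regional mean having the same standardised effect as a single voxel. Dilution within the region would narrow the gap. That regional tests are excluded altogether is an inference from the wording, though a well-supported one. Inflated effect sizes are a risk that the plan leaves open; the article does not commit to producing them. The change is advisable because it is cheap and serves the pilot's own aim.

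**What to change.** - Add the anatomical bilateral amygdala mean (food minus non-food) as the pre-specified test of the amygdala hypothesis. Take the region from the FreeSurfer segmentation already run and analyse one value per visit in the mixed model already planned for extracted scores.
- Report its estimate and confidence interval whatever the significance, and use that estimate for planning later studies.
- Name specific prefrontal and superior parietal regions for the task-switching contrasts and report their estimates as supporting.
- Keep the whole-brain analysis for exploratory results outside these regions.
- Delete the sentence that justifies whole-brain analysis as protection against bias.

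The cost is wording and some extraction from data already planned, with no new scans. The downsides are a few additional named tests, possible dilution of a focal effect within a region, and no remedy for the low power at n = 20.

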
## Methods

### Participants

Participants for this study will be recruited directly from an existing RCT. The RCT is testing an adaptation to standard FBT wherein adolescents who do not gain 2.4 kg by session 4 are randomly assigned to either continue standard FBT or to receive Intensive Parent Coaching (IPC) which involves an additional intense scene during session 4 to increase urgency to act in the parents, a parent-only session to further support parental behavior change for refeeding, and an additional family meal for greater support and guidance of parent refeeding behaviors. Prior research informed the selection of 2.4 kg as the marker of early treatment response. Five studies identified early weight gain in FBT as a possible marker of early treatment response (2–4, 6, 49) converging on a consistent weight gain range of 2–3 kg by session 4. Unpublished data on early response from the largest multi-site study of FBT for adolescent AN (2) matched the weighted average of the current published studies, a weight gain of 2.4 kg by session 4. An additional study by Hughes and colleagues (50) found that 2.8 kg by session 5 was the most sensitive predictor of remission. However, this study involved twice weekly sessions for the first 2 weeks with session 5 occurring on week 3 of treatment (unlike 1 session per week in other trials). This increased intensity of treatment delivery may have shifted the timing and amount of early weight gain predictive of remission by end of treatment (50). Thus, the proposal settled on 2.4 kg by session 4 as the marker of early response. Importantly, we considered the use of change in percentage ideal body weight or BMI-SDS (body mass index standard deviation score) per age, but the prior research showed these predictive effects with the actual weight gained regardless of initial weight, height, age, or sex.

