### Procedure

Assessments for the main RCT will be conducted at six major timepoints (baseline, 3-month mid-treatment, EOT (maximum of 9 months), and at 6- and 12-month follow-up). These assessments will include measures of weight, parental measures, and other psychopathology variables. Weekly assessment of weight and parent factors will also be conducted. For the neuroimaging study, we invite participants to have MRI and fMRI scans at baseline, session 4 mid-treatment, and EOT. All assessors are trained to reliability in the Eating Disorder Examination (EDE) (51) and other clinical diagnostic interviews, including the Kiddie Schedule for Affective Disorders and Schizophrenia (K-SADS) (52).

Neuroimaging sessions consist of structural, diffusion-weighted, and functional scans (one resting-state and two task-based). We use a 3T GE signa scanner to collect functional and anatomical imaging data. Visual stimuli are presented with a digital projector/reverse screen display system. Echo spiral imaging is used to measure the blood oxygen level dependent (BOLD) signal as an indication of cerebral brain activation. Images consist of 31 axial slices (4.0 mm with 0.5 mm gap) covering the whole brain (RT = 2 s, echo time = 30 ms, flip angle = 80, interleave = 1, FOV = 22 cm, matrix = 64 × 64). To reduce blurring and signal loss from field inhomogeneities, an automated high-order shimming method based on spiral acquisitions is used before acquisition of functional scans. R-fMRI scans consist of 240 volumes acquired over 8 min. Functional scans during the task-based paradigms will be acquired over approximately 22 min (task switching) and 8 min (food image task). Motion is measured immediately following functional scans, and the experiment is rerun if motion exceeds 1 mm. A diffusion-weighted scan (DTI) is collected with 37 diffusion directions (FOV = 22 cm, 2.3 mm slices). A high-resolution T1-weighted three-dimensional inversion recovery spoiled gradient-recalled acquisition in the steady state MRI sequence is used (inversion time = 400 ms, RT = 8 ms, echo time = 3.6 ms, flip angle = 151, FOV = 24 cm, 124 slices in coronal plane, matrix = 256 × 192, number of excitations = 2; acquired resolution = 1.5 × 0.9 × 1.1 mm). Images are reconstructed as a 124 × 256 × 256 matrix. We preprocess all data within 1-week of the scan to ensure that all the data are usable. We rescan subjects for whom we have poor data on structural and resting state scans.

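### The primary early-responder contrast compares self-formed groups, and the article states no term for baseline nutritional status, so change that depends on the starting deficit could be credited to early weight gain

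*Protocol article*

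**What the plan says.** The closing paragraphs of the Data Analytic Plan define the contrast: "Primary comparisons will be conducted between those who gain 2.4 kg by session 4 and those who do not (early responders vs. non-early responders"). They apply repeated-measures or mixed models to every outcome: volumes, surface area, thickness, connectivity, DTI measures, task contrasts and risk-taking. One covariate is named, with its reason: "Because EOT will occur at different times after baseline depending on treatment duration, time will be included as a covariate". Weight change will also be used as a continuous variable, "particularly if we have small cell size in one of the two responder groups".

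Participants shows where randomisation sits in the parent trial: "adolescents who do not gain 2.4 kg by session 4 are randomly assigned to either continue standard FBT or to receive Intensive Parent Coaching (IPC"). It therefore acts only within the non-responders. The same section explains the use of kilograms rather than percent ideal body weight or BMI-SDS: earlier studies found prediction from "the actual weight gained regardless of initial weight, height, age, or sex".

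Other baseline information appears in the DTI paragraph, which notes that dehydration can affect DTI and structural data. It says "we will include reports of hydration, as well as recent hospitalizations, as many of the patients in the trial were in the hospital for medical" stabilisation before enrolment. How these reports enter a model is not stated.

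**The concern.** Responder status is an outcome of the first weeks of treatment. Any baseline characteristic that is related to both weight gained and brain change confounds the comparison. Baseline nutritional status is the obvious candidate. The Introduction describes structural deficits that recover with nutrition, so the room for recovery plausibly depends on the size of the deficit.

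Repeated measures remove stable differences in level between patients. They do not remove a rate of change that depends on where the patient started. The continuous weight-change analysis is exposed in the same way.

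The argument for kilograms concerns prediction of clinical outcome. It does not show that brain change is independent of initial weight.

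Two uses of the result are at stake. The study is meant to supply preliminary effect sizes for later research. Specific Aims and Hypotheses also reads the DTI contrast as evidence that better nutrition acts quickly on the brain, and the Discussion hopes such evidence will motivate parents.

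**Working it through.** The plan has no figure of its own to reproduce. The target is "The target sample size for this preliminary study is 20 in order to establish feasibility of including neuroimaging to an RCT of FBT" and to obtain preliminary effect sizes, with no alpha, power, SD or correlation given. The inputs below are therefore assumptions, except N = 20 and the definition of the contrast.

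**Closed form, no true effect of weight gain**

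Let a be the correlation of baseline depletion with weight gained, and b its correlation with brain change. The spurious correlation between gain and brain change is a × b. Cutting gain at its median multiplies this by 0.798, and d = 2r/√(1 − r²).

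| a | b | r = 0.798ab | d |
|---|---|---|---|
| 0 | any | 0 | 0 |
| 0.3 | 0.3 | 0.072 | 0.14 |
| 0.4 | 0.5 | 0.160 | 0.32 |
| 0.5 | 0.5 | 0.200 | 0.41 |
| −0.5 | 0.5 | −0.200 | −0.41 |

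The last row is the case in which more depleted patients gain less; a real effect would then be masked.

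The plan uses a fixed 2.4 kg cut, not a median. For a 5/15 split with a = b = 0.5, the normal density at the 25% cut is 0.318 and √(0.25 × 0.75) = 0.433. So r = (0.318/0.433) × 0.25 = 0.184, and d = (0.184/0.433)/√(1 − 0.184²) = 0.43. The split makes little difference.

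For the continuous analysis the spurious correlation is ab itself, at most 0.25 in this range.

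**Simulation, 10 versus 10, 6,000 runs per setting, no true effect**

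Responders start g SD lower in nutritional status, and brain change correlates rho with depletion. The adjusted model has baseline status plus one unrelated age-like covariate.

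| rho | g | Unadjusted bias (SD) | Unadjusted type I error | Adjusted bias (SD) | Adjusted type I error |
|---|---|---|---|---|---|
| 0 | 1.0 | 0.00 | 4.7% | 0.00 | 4.8% |
| 0.5 | 0 | 0.00 | 4.8% | 0.00 | 5.0% |
| 0.3 | 0.5 | 0.16 | 6.5% | 0.01 | 5.4% |
| 0.3 | 1.0 | 0.31 | 10.0% | 0.01 | 4.9% |
| 0.5 | 0.5 | 0.25 | 8.6% | 0.00 | 5.0% |
| 0.5 | 1.0 | 0.51 | 19.4% | 0.02 | 5.3% |

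The two approaches agree. By the formula above, a = 0.3 corresponds to a group gap of about 0.49 SD, and a = 0.5 to about 0.87 SD. If either link is zero, there is no bias.

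**Precision**

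The standard error of a 10 versus 10 difference is √(1/10 + 1/10) = 0.45 SD. In the simulation, adjustment moved the SD of the estimate from 0.445 to 0.540 when rho = 0 and g = 1. It moved it from 0.448 to 0.342 when rho = 0.7 and g = 0. So adjustment can cost or gain precision.

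**The case against.** The strongest objection is that the article is a condensed account. The sentence on time need not be a full covariate list, and a statistical analysis plan may hold the rest. That stands as far as it goes: a reader might infer that the plan excludes baseline adjustment, and the text does not say so. The point survives because the article does fix the outcomes, the model type, the primary contrast and one covariate with its reason. That reason concerns EOT, so the session-4 contrast is left with no stated control.

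A reader might also infer that early responders start more depleted and that the result will be inflated. No figure in the documents supports this; the bias could be zero or reversed.

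Hydration and hospitalisation reports are a partial proxy for baseline state and are to be included. This also stands. However, they are raised for DTI and structural data only, with no stated role in a model and no link to the resting-state, task or risk-taking outcomes.

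It might seem that age needs adjustment throughout because of the 12–18 range. Session 4 comes only weeks after baseline, so normal development has little time to act. Age matters more at EOT, at about 6 to 9 months.

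Finally, this is a feasibility pilot with exploratory hypotheses, and a bias of 0.4 is no larger than one standard error at 10 versus 10. That limits the harm to any single test. It does not help effect sizes carried forward, because this bias does not shrink as the sample grows.

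**Conclusion.** The concern holds in a limited form. The primary contrast is between non-randomised groups, and the article states no term for baseline nutritional status, so change that depends on the starting deficit could be attributed to early weight gain. The magnitude is illustrative only: from 0 to about 0.4 SD in either direction for correlations of 0 to 0.5 on each link, none of which the documents supply. The removal of bias in the simulation also assumes that the measured baseline value captures the confounding. This is a recommended improvement to the analysis, not a demonstrated error in a result.

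**What to change.** For each outcome, report two estimates of the baseline-to-session-4 contrast side by side: the planned one, and one adjusted for centred baseline %EBW and its interaction with visit. The interaction is needed because a main effect alone adjusts level, not change. Do the same for the continuous weight-change analysis. Add age, with its visit interaction, for the EOT analysis only. State that recent hospitalisation enters the same adjusted model if numbers allow. Describe the responder contrast as an association.

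The change is mainly analysis wording. Procedure lists weight among the assessments, and the Introduction uses %EBW as its measure of weight restoration. Height is not listed, so its availability at baseline should be confirmed.

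On a simple session-4 change score, one covariate takes one residual degree of freedom (18 to 17 with 20 complete pairs), and hospitalisation takes another. In a three-visit model each covariate adds three parameters (one main effect and two visit interactions), which is why the list should stay short. Some precision is lost if baseline status is unrelated to change.
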